#### Secondary analyses

The secondary outcome of TF prevalence will be analysed in exactly the same manner as the primary outcome, except that we will adjust for baseline TF prevalence rather than *Ct*. The effectiveness of each intervention on *Ct* prevalence will be assessed separately, first comparing each trial arm with the control separately (accounting for the matching in comparing the F&E arms, by adjusting for matched pair in stage (1) then using a factorial-style approach (comparing arms 1 and 2 with arms 3 and 4 and comparing arms 1 and 3 with arms 2 and 4). The same two-stage approach employed for the primary comparison (with additional adjustment for the analysis of each intervention for the other in the factorial-style analysis) will be used.

Primary analysis of behavioural outcomes will be conducted on an ITT basis to assess whether the intervention was effective as delivered. Analysis will be adjusted for baseline levels of behaviour. Planned subgroup analysis will be done according to water access, level of education and socioeconomic status. If intervention reach is suboptimal or variable across clusters, per-protocol analyses will be performed to assess whether the intervention succeeded in changing behaviour among those directly exposed to it and subgroup analysis comparing intervention outcomes according to level of intervention exposure will also be performed. The two-stage approach will be followed as above.^23^ The costs of all aspects of the intervention will be tabulated for use in a cost analysis.

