### Randomisation and assignment of interventions

This study involves 68 clusters, with 17 allocated to each trial arm. MDA takes place at the zone level, to ensure an adequate treatment buffer zone between clusters, however, the household-level F&E intervention was anticipated to be too intensive to deliver to such a large area within the context of the trial, so a two-stage approach to randomisation was taken. First, 34 zones (within kebeles) were selected based on having a high prevalence of TF in children aged 1–9 years during screening surveys. Within each zone two clusters were identified; a cluster comprises 2–3 garees (approximately 90 households collectively). The 34 zones were randomly assigned to receive either standard or enhanced antibiotic (with 17 zones receiving each option), and randomisation was restricted to ensure balance between arms in terms of TF prevalence and geographical location. The two clusters within each zone were then randomised to either standard or enhanced F&E. The randomisation sequence was generated by the trial statistician using Stata V.17.

Additionally, clusters receiving enhanced antibiotic will have a buffer zone comprising the zone of the kebele around the two clusters in that arm. Standard SAFE (including standard antibiotic) will be implemented by the national trachoma elimination programme in all settlements in surrounding buffer zones with the additional aim of minimising spillover effects (online supplemental file 2).

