### Statistical considerations and data analysis

#### Sample size for primary outcome

17 clusters per arm, with a sample of 60 children/cluster, gives 90% power and 95% confidence to detect an absolute difference of 4% between the control (standard SAFE) (5%) and intervention (stronger SAFE) (1%) arms, assuming a design effect of 2.5 (intracluster correlation less than 0.025, estimated from previous data^30^ and an expected cluster-level *Ct* prevalence range 0%–14%). This would also provide good power for other pairwise comparisons by arm, and at different time points. The sample size considerations for key secondary outcomes are included in online supplemental file 3.

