#### Primary analysis

The primary analysis will be a comparison between the control arm (standard SAFE (arm 1)) and the arm receiving both enhanced F&E and enhanced antibiotic (stronger SAFE (Arm 4)). Primary analyses will be by intention to treat (ITT), with clusters/participants analysed according to the arm to which they were randomised with adjustment for baseline *Ct* prevalence.

The intervention effect on *Ct* prevalence will be estimated as a risk difference and 95% CI, estimated using a two-stage approach and adjusted for baseline prevalence of *Ct*. First a logistic regression will be fitted with baseline cluster *Ct* prevalence as an exposure and presence of *Ct* at end line as the outcome. The residuals of this regression will be used in an unpaired t-test to obtain the adjusted risk difference and the associated CI in a two-stage approach recommended by Hayes & Moulton.^23^

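### Secondary Ct comparison of arm 2 with arm 1: fixed pair terms in stage 1 followed by an unpaired t-test understate the standard error by √2, so the nominal 5% test runs at about 17%

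*Protocol article*

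**What the plan says.** All places are in the protocol article.

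- *Randomisation and assignment of interventions*, antibiotic: "The 34 zones were randomly assigned to receive either standard or enhanced antibiotic (with 17 zones receiving each option").
- Same section, F&E: "The two clusters within each zone were then randomised to either standard or enhanced F&E". Each zone is therefore a matched pair for F&E: 17 pairs for arm 2 v arm 1, 17 for arm 4 v arm 3, and 34 in all.
- *Primary analysis*, stage 1: "First a logistic regression will be fitted with baseline cluster" Ct prevalence as the covariate.
- *Primary analysis*, stage 2: "The residuals of this regression will be used in an unpaired t-test to obtain the adjusted risk difference and the associated CI".
- *Secondary analyses*, each arm against control: "accounting for the matching in comparing the F&E arms, by adjusting for matched pair in stage (1").
- *Secondary analyses*, factorial F&E contrast: "comparing arms 1 and 3 with arms 2 and 4", with additional adjustment named only for the other intervention.
- *Secondary analyses*, test: "The same two-stage approach employed for the primary comparison" is to be used.

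The article states no paired second stage, variance correction or change in degrees of freedom for the matched comparison.

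**The concern.** There are two sound ways to use the pairing: analyse within-pair differences, or fit pair terms and base the inference on a variance that allows for them. The text does half of the second. It removes the pair effect in stage 1, then passes the residuals to a test that assumes 34 independent values. Fitting pair terms makes the two residuals in a pair mirror images, so only 17 independent quantities remain, and the unpaired variance formula is wrong for them.

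Arm 2 v arm 1 is the comparison that isolates enhanced F&E under standard antibiotic. With a standard error that is too small, a chance difference would be declared an effect more than three times as often as the stated error rate allows (16.9/5 = 3.4), and the interval around the F&E effect would be too narrow.

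**Working it through.** **Inputs.** 17 pairs for arm 2 v arm 1 and 34 for the factorial F&E contrast (*Randomisation*). From *Sample size for primary outcome*: 60 children per cluster, two-sided 5%, 5% v 1% prevalence, design effect 2.5 and intracluster correlation up to 0.025. The within-zone correlation is not given, so it is varied below as an assumption.

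**The plan's own figure.** The article gives no operating characteristic for the F&E comparison. Its 90% power is for the primary comparison: "17 clusters per arm, with a sample of 60 children/cluster, gives 90% power and 95% confidence to detect an absolute difference of 4"%. The effective sample size per arm is 17 × 60 / 2.5 = 408. The null SE is √(2 × 0.03 × 0.97 / 408) = 0.01194 and the alternative SE is √((0.05 × 0.95 + 0.01 × 0.99) / 408) = 0.01186. Then z = (0.04 − 1.96 × 0.01194) / 0.01186 = 1.40, a power of 91.9%. The stated 90% is reproduced within two points, so the inputs are read correctly.

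**Algebra of the test as written.**

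1. A logistic model with a term for each pair has score equations that make observed equal expected within each pair. This holds with baseline prevalence also in the model.
2. With equal cluster sizes, the two cluster-level residuals in a pair are therefore +d/2 and −d/2, where d is the (baseline-adjusted) within-pair difference.
3. With m pairs, the difference in mean residuals is the mean of d, and its correct variance is s_d²/m.
4. The unpaired test takes each arm's residual variance as s_d²/4 and computes 2 × (s_d²/4)/m = s_d²/(2m), half the correct value.
5. Hence t(unpaired) = √2 × t(paired), whatever the prevalence, intracluster correlation or within-zone correlation.

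**Size of the nominal 5% test.** This is P(|t with m−1 df| > t(0.975, 2m−2)/√2).

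| Contrast | Threshold | Size |
|---|---|---|
| Arm 2 v arm 1, m = 17 | 2.037/1.414 = 1.440 | 16.9% |
| Same, with the 16-df critical value | – | 15.3% |
| Factorial F&E, m = 34, only if pair were also fitted there | 1.997/1.414 = 1.412 | 16.7% |

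Coverage for arm 2 v arm 1 is 100 − 16.9 = about 83%. Correcting the degrees of freedom alone does not cure it.

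**Simulation.** Beta-binomial clusters were used, with 60 children, intracluster correlation 0.025 and 17 pairs.

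- With pair and baseline prevalence fitted (5% prevalence, assumed within-zone correlation 0.4, 2,000 runs), the unpaired test rejected in 16.8% and a paired test on the same residuals in 4.8%. The ratio of the two t statistics was 1.4142 in every run.
- Without the baseline covariate (prevalence 1–5%, assumed correlation 0 or 0.5), the unpaired test rejected in 16.9–18.0% and the paired test in 3.8–4.9%.
- With 60–80 children per cluster the SE ratio was 1.41 and the size 17.0%.

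**Pairs with no infection.** Their pair term has no finite estimate. They averaged about 0.4 of 17 at 5% prevalence and 3.6–3.9 of 17 at 2%. Depending on the software they are dropped or get zero residuals. Neither removes the inflation: it was 18.0% with such pairs dropped at 3% prevalence.

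**Factorial F&E contrast as written.** Pair is not fitted and the test is unpaired. If residuals within a zone have correlation ρ, the true variance is (1 − ρ) times the one used, so the CI is 1/√(1 − ρ) too wide: 5% at ρ = 0.1 and 20% at ρ = 0.3. In simulation with 34 pairs, 60 children and 1–5% prevalence, the size was 2.0–2.4% at an assumed correlation of 0.5 between the underlying prevalences in a zone.

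**The case against.** The strongest reply is that the unpaired test is named only for arm 4 v arm 1, which is not a within-zone comparison, and reaches the matched comparison by back-reference. The article is condensed, the SAP is not shown, and the authors may intend a paired second stage. If so, the inflation vanishes. That stands as a possibility, but the article names both steps, and a programmer following it would get the wrong interval. The text needs correcting either way.

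A second reply is that the article does not say the pair terms are fixed. If pair were a random effect and its predicted value removed, the inflation would be smaller: 6.0%, 8.2% and 10.8% at assumed within-zone correlations of 0.1, 0.3 and 0.5 (normal-theory simulation, 17 pairs, variance components taken as known). This stands. The 17% belongs to the fixed-effect reading and is the upper case, although the test is too liberal under both.

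A reader might also infer more than the text supports:

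- *Every F&E standard error is too small.* The factorial F&E contrast, as written, omits pair and errs the other way if zones are positively correlated.
- *The trial's main result is affected.* Arm 4 v arm 1 and arm 3 v arm 1 compare clusters from different zones, so no pairing arises.
- *TF and fly outcomes share the fault.* TF is to be analysed like the primary outcome, which is arm 4 v arm 1. The article states no second-stage test for fly outcomes.
- *The trial's promised contribution on F&E rests on this contrast.* The Introduction attaches that contribution to the behaviour change, process and entomological outcomes, and the stated aim is stronger SAFE against current standard approaches.

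**Conclusion.** The concern holds for one secondary contrast, arm 2 v arm 1 on Ct. As written, the standard error is too small by √2, the nominal 5% test has a size of about 17%, and the 95% CI covers about 83%. This rests on pair entering stage 1 as fixed terms, on the unpaired second stage carrying over as the text says, and on roughly equal numbers of children per cluster. It does not depend on the prevalence or on the within-zone correlation.

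The factorial F&E contrast has a separate and milder fault. It ignores the pairing, and its interval is too wide if clusters in a zone are positively correlated, a correlation the article does not give. Adding pair to its stage 1 while keeping the unpaired test would raise its size to about 16.7%.

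This should be fixed before the Ct results are analysed. It does not threaten the trial's primary conclusion.

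**What to change.** For comparisons by F&E allocation within zones, state one method:

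- Stage 1: logistic regression on baseline prevalence only, without pair terms.
- Stage 2: for each zone, take the enhanced minus standard F&E difference in cluster-level residuals and apply a paired t-test, with 17 − 1 = 16 df for arm 2 v arm 1 and 34 − 1 = 33 df for the factorial F&E contrast.

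A paired test on pair-adjusted residuals would also hold its size (4.8% in the simulation above). Leaving pair out of stage 1 is preferable because it keeps the pairs with no infections. The unpaired test stays for arm 4 v arm 1 and arm 3 v arm 1.

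Use the same paired second stage for behavioural outcomes wherever the two-stage approach is applied to clusters compared by F&E allocation, since the article refers those analyses back to the same method.

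The cost is a few sentences in the analysis plan and a small change in code. No new data are needed. The Trial status section reports laboratory analysis still under way, so the change should be dated and recorded before the Ct results are analysed.

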### Trial interventions

#### Antibiotic intervention (A)

Within kebeles, zones were allocated to an antibiotic intervention arm. Each *zone* includes two trial clusters.

Azithromycin is donated to the national trachoma control programme by the manufacturer (Pfizer) through the International Trachoma Initiative. In antibiotic MDA, individuals aged ≥6 months will be offered height-based treatment with azithromycin, delivering approximately 20 mg/kg to a maximum dose of 1 g. Children below the age of 6 months will be given tetracycline eye ointment instead of azithromycin, in accordance with national policy for trachoma elimination.

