##### Enhanced antibiotic (arms 3 and 4)

17 zones (34 clusters, 2 clusters per zone) were randomised to receive annual enhanced antibiotic, where an additional single dose of oral azithromycin (20 mg/kg up to a maximum dose of 1 g) will be given 2 weeks after the initial programmatic MDA (delivered as described above) to all individuals above the age of 2 years for three annual rounds in accordance with Ethiopian national regulatory body requirements.

MDA in all arms is directly observed and recorded. MDA is delivered by the regional trachoma elimination programme. Our study team is embedded within the distribution team to support data collection during distribution.

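### The factorial antibiotic contrast is analysed by cluster although antibiotic was randomised by zone, so its confidence interval can be too narrow

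*Protocol article*

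**What the plan says.** **Allocation.** Under Randomisation and assignment of interventions: "The 34 zones were randomly assigned to receive either standard or enhanced antibiotic (with 17 zones receiving each option". Under Antibiotic intervention (A): "Each *zone* includes two trial clusters". The enhanced-antibiotic section gives the same structure: "17 zones (34 clusters, 2 clusters per zone) were randomised to receive annual enhanced antibiotic". F&E was allocated one level lower: "The two clusters within each zone were then randomised to either standard or enhanced F&E". The zone allocation was also constrained: "randomisation was restricted to ensure balance between arms in terms of TF prevalence and geographical location".

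**Analysis.** Secondary analyses sets out the factorial contrasts, "comparing arms 1 and 2 with arms 3 and 4 and comparing arms 1 and 3 with arms 2 and 4", and the method: "The same two-stage approach employed for the primary comparison (with additional adjustment for the analysis of each intervention for the other". That approach is defined under Primary analysis. A logistic regression on baseline cluster *Ct* prevalence comes first, and then: "The residuals of this regression will be used in an unpaired t-test to obtain the adjusted risk difference and the associated CI". Adjustment for matched pair is mentioned only for comparisons of the F&E arms.

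**The concern.** This is a split-plot design. The zone is the experimental unit for antibiotic, and the cluster within a zone is the unit for F&E. Both clusters of a zone always carry the same antibiotic allocation and share the zone-level drug distribution, so they are not two independent replicates of that allocation.

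For arms 1+2 v 3+4, the primary method carried over with 17 clusters per arm has 68 units and 66 degrees of freedom. Only 34 units were randomised, which gives 32. The extra adjustment for F&E does not help, because each zone has one cluster at each F&E level. Nor can the matched-pair adjustment be borrowed: zone determines the antibiotic arm, so zone terms in stage 1 would absorb the effect being estimated.

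At stake is the pooled estimate of enhanced antibiotic in a trial whose Introduction aims at robust evidence for programme managers and policy-makers. Its precision may be overstated.

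**Working it through.** **Inputs from the protocol.** 34 zones (17 v 17), 2 clusters per zone, 17 clusters per arm, 60 children per cluster, control prevalence 5%, intervention 1%, design effect 2.5, intracluster correlation below 0.025.

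**Not in the protocol.** The correlation ρ between the stage 1 residuals of the two clusters in a zone. It is assumed here, and a range is shown.

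**1. The plan's own figure.** The only stated power is for arm 4 v arm 1. Effective sample per arm = 17 × 60 / 2.5 = 408. A two-sided 5% test of 5% v 1% then has 91.9% power, against the stated 90%. The design effect also agrees: 1 + 59 × 0.025 = 2.475. The inputs are therefore sound. No figure is given for the factorial antibiotic contrast.

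**2. Variance for arms 1+2 v 3+4.** Let s² be the variance of a cluster residual.
- Assumed by a 34 v 34 test, per side: s²/34.
- Actual, with 17 zones of two correlated clusters: s²(1+ρ)/34.
- Ratio of true to computed standard error: √(1+ρ).
- Approximate type I error: 2[1 − Φ(1.96/√(1+ρ))].

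Critical t values are 1.997 (66 df) and 2.037 (32 df).

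| ρ (assumed) | True SE / computed SE | Type I error, formula | Type I error, simulation, 34 v 34 clusters | CI of 17 v 17 test relative to 34 v 34 |
|---|---|---|---|---|
| 0 | 1.00 | 5.0% | 5.0% | about 2% wider |
| 0.1 | 1.05 | 6.2% | 6.3% | 7% wider |
| 0.2 | 1.10 | 7.4% | 7.5% | 12% wider |
| 0.3 | 1.14 | 8.6% | 8.6% | 16% wider |
| 0.5 | 1.22 | 11.0% | 11.2% | 25% wider |

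The simulation used normal cluster summaries with no antibiotic effect, 200,000 runs per value. The 17 v 17 test stayed at 4.9–5.1% throughout.

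**3. Binary data without baseline adjustment.** 68 clusters of 60 children, 5% prevalence, intracluster correlation 0.0254, 20,000 runs per row. The share of between-cluster variance lying at zone level is assumed.

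| Zone share | Implied correlation of cluster prevalences | 34 v 34 | 17 v 17 |
|---|---|---|---|
| 0% | 0 | 4.9% | 4.8% |
| 25% | 0.14 | 6.4% | 4.7% |
| 50% | 0.28 | 8.2% | 4.9% |
| 75% | 0.44 | 9.7% | 4.5% |
| 100% | 0.61 | 12.8% | 4.8% |

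**4. Binary data with baseline adjustment, as the plan specifies.** With 25–90% of between-cluster variance at zone level, the 34 v 34 test gave about 6–10% when the baseline adjustment was moderate and 6–8.5% when it was strong; the zone-level test stayed at about 5%. A separate set (3,000 runs per scenario, zone share 30–90%) gave 5.4–7.4%, with 4.2–5.2% for the zone-level test. The size depends on how well baseline prevalence predicts the endpoint. The direction does not change.

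**5. Which contrasts are affected.** Arm 4 v arm 1 and arm 3 v arm 1 each take one cluster per zone, so cluster and zone coincide (17 v 17). For the factorial F&E contrast, ignoring the pairing would err the other way: type I error of about 3.0% at ρ = 0.2 and 0.7% at ρ = 0.5.

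**The case against.** **The protocol never prints 34 v 34 or 66 degrees of freedom.** It only carries the primary method over, and there the cluster and zone units coincide. The sentence on matching has an unclosed bracket, the article is condensed, and it commits to CONSORT guidance for cluster trials. This stands in part: the cluster-level unit is an inference. It is nevertheless the natural reading of a stated method. The only addition named is adjustment for the other intervention, and a general reporting commitment does not set the unit of analysis.

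**ρ may be small.** This stands. Baseline *Ct* adjustment removes some shared variation, and at ρ = 0 there is no inflation. But the protocol itself treats the two clusters as matched, and nothing in it implies independence.

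**Restricted randomisation offsets the inflation.** This stands in part. Balancing zones on predictors of outcome makes a t-test that ignores the restriction conservative. In a simulation without baseline adjustment, keeping the best 10% of allocations on one zone-level covariate with half the between-cluster variance at zone level, 8.1% fell to 7.9%, 6.8% and 5.7% when the covariate correlated 0.3, 0.5 and 0.7 with the zone effect. With a quarter at zone level, 6.8% fell to 6.5%, 5.8% and 4.7%. These correlations are assumptions. The restriction usually reduces the inflation rather than removing it, and it made the zone-level test somewhat conservative (3.2–4.5% in the half-share case).

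**Only a secondary contrast is touched.** This stands, and it limits the severity.

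**Conclusion.** The point holds conditionally. As written, the method for arms 1+2 v 3+4 does not respect the unit to which antibiotic was randomised. For an assumed residual within-zone correlation of 0.1 to 0.5, the true standard error is about 5–22% larger than the one computed, and type I error is roughly 6–11% (about 6–10% in most simulations with baseline adjustment, somewhat lower in one set).

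A reader might infer that the interval is certainly too narrow and the error rate certainly above 5%. The documents do not support that: they give no ρ, and the restricted allocation can pull the error back towards 5%. A reader might also infer that the trial's main conclusion is at risk. It is not, because the primary comparison uses one cluster per zone, and the planned arm 3 v arm 1 comparison gives an unaffected estimate of enhanced antibiotic alone. The plan should be corrected, but this is not critical to the primary result.

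**What to change.** For arms 1+2 v 3+4, keep stage 1 with baseline adjustment, average the two cluster residuals within each zone, and run the unpaired t-test on 17 v 17 zone means (32 df, less any zone-level covariates). F&E is balanced within zones, so it needs no further adjustment here. A model with a zone random effect and small-sample degrees of freedom would be an alternative.

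State explicitly that the zone is the unit of analysis for antibiotic and the within-zone difference is the unit for F&E. This also settles how far the matched-pair sentence reaches.

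The cost is a sentence in the analysis plan and a few lines of code. No new data are needed, and Trial status reports laboratory analysis still under way. The interval for this contrast widens by about 7–25% for ρ of 0.1 to 0.5, and by about 2% if ρ is zero. Under the restricted allocation it may be slightly conservative.
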